### 2.3 Procedures

All procedures, including registration, consent, survey completion, and a two-week retest, administered to approximately 140 participants with mental disorders to evaluate the test–retest reliability of the five-item Japanese version of the Distress Questionnaire (DQ5-J), will be conducted online. Among retest completers, participants who report “no change” on the Patient Global Impression of Change at the two-week retest will be retained for the primary test–retest reliability analysis. Participation in the survey will be voluntary. Participants who complete the survey will receive points equivalent to 200 yen (approximately US $
1.30) and those who complete the retest will receive an additional 100-yen worth of points (approximately US $
0.65).

### 2.4 Measures

The registry will incorporate standardized assessments of QOL and related psychosocial factors, psychiatric symptoms, sleep characteristics, and attitudes toward digital health technology. The following measures will be used. To measure QOL and related psychosocial factors, we will use the DQ5-J, six-item Kessler Psychological Distress Scale (K6) [40], EuroQoL 5 Dimensions 5-Level (EQ-5D-5L) [41,42], Satisfaction With Life Scale (SWLS), short form of the Metacognitions Questionnaire-Short Form (MCQ-30; only the positive beliefs about worry and the negative beliefs about uncontrollability and danger of worry subscales) [43,44], Effortful Control Scale (EC; only attention control subscale) [45,46], Cognitive Attentional Syndrome Scale-1 Revised (CAS-1R; only the coping strategies subscale) [47,48], Shift-and-Persist coping strategy (SAP) [49,50], subjective Socioeconomic Status (SES; childhood and current) [23,24,25], and the Brief Parental Burnout Scale (BPBs) [26]. To measure sleep characteristics, we will use the Insomnia Severity Index (ISI) [51,52], Regularity, Satisfaction, Alertness, Timing, Efficiency, Duration of Sleep Scale (RU-SATED) [53,54], Reduced Morningness–Eveningness Questionnaire (rMEQ) [55,56], Dysfunctional Beliefs and Attitudes about Sleep Scale (DBAS-16) [57,58], Ford Insomnia Response to Stress Test (FIRST) [59,60], Anxiety and Preoccupation about Sleep Questionnaire (APSQ) [61,62], Bedtime Procrastination Scale (BPS) [63,64], and Sleep Hygiene Practice Scale (SHPS) [65,66]. To measure psychiatric symptoms, we will use the Patient Health Questionnaire-9 (PHQ-9) [67,68], Generalized Anxiety Disorder-7 (GAD-7) [69,70], Liebowitz Social Anxiety Scale (LSAS) [71,72], Anxiety Sensitivity Index-3 (ASI-3) [38,73], Impact of Event Scale-Revised (IES-R) [74,75], Obsessive/Compulsive Inventory-Revised (OCI-R) [76,77], short form of the Autism-Spectrum Quotient (AQ-28) [78], and Adult ADHD Self-Report Scale (ASRS) [79]. To measure attitudes toward digital health technology, we will use the eHealth Literacy Scale (eHEALS) [80,81], Japanese version of the e-Therapy Attitudes and Process Questionnaire (eTAP-J) [82], and Attitudes toward Safety, Support, Understanding, and Risk for Human-AI therapists (ASSURE; two parallel scales: ASSURE-HT and ASSURE-AI), AI romance ethics, Anthropomorphism [83], Fulfilling emotional needs [84,85], Relationship Authenticity (RA) [86], and Desire for Real-World Relationships (DRR) [86]. Additionally, we will collect basic demographic characteristics, including age, sex, region of residence, occupation, marital status, fertility status, income status, and educational level. The survey consists of 1–40 items per page across 45 pages, and all items are mandatory.

### 2.5 Study Aims and Analytic Strategy

Table 1 summarizes the three aims, sub-studies, outcomes, and planned analyses; the full analytic specifications are provided in the **Supplementary Materials**. Consistent with the AHRQ User’s Guide for Patient Registries, which notes that a registry may serve multiple stated purposes [12] but that its overall purpose should be translated into specific objectives or research questions, no single clinical primary outcome is defined for the registry as a whole; rather, the registry-level objective is to establish a harmonized transdiagnostic PROs infrastructure. Therefore, each sub-study has its own analytic objective, study population, key variables, and key outcomes (Table 1). Conceptually, the sub-studies are organized into foundational psychometric validation, hypothesis-driven association analyses, and exploratory profiling analyses; this grouping reflects their analytic role rather than a temporal order. The distinction between confirmatory and exploratory analyses is explicitly indicated in the “Analysis type” column of Table 1. Confirmatory analyses are based on prespecified hypotheses, whereas exploratory analyses are hypothesis-generating in nature. Therefore, findings from exploratory analyses should be interpreted with caution. Replication must be conducted in future studies before firm conclusions can be drawn.

**Table 1. T001:** **Overview of the study aims, populations, objectives, key variables, analysis plans, and analysis types**.

Study aim/Sub-study	Population	Objective/Hypothesis	Key variables	Analysis plan	Analysis type
**Aim 1. Psychosocial correlations and measurement foundations for QOL and psychiatric symptoms**					
1a. DQ5-J validation	Patients with mental disorders	Examine the reliability and validity of the DQ5-J.	Target instrument: DQ5-J Validation measures: PHQ-9, GAD-7, EQ-5D-5L	Structural validity: CFA first, EFA only if needed Reliability: Internal consistency (*α*, *ω*), Test–retest (intraclass correlation coefficient) Construct validity: Convergent/discriminant/known-groups validity testing Criterion validity: receiver operating characteristic/area under the curve analysis	Confirmatory
1b. Parental burnout in relation to socioeconomic status, mental health, and sleep	Patients with mental disorders	Examine the associations of BPBs with current SES, psychiatric symptoms, neurodevelopmental traits, sleep measures, and QOL.	Exposure: BPBs Correlates/outcomes: current SES, psychiatric symptoms (e.g., PHQ-9, GAD-7, K6), neurodevelopmental traits (e.g., AQ-28, ASRS), sleep measures (e.g., ISI, RU-SATED), and QOL (e.g., SWLS and EQ-5D-5L)	Pearson/Spearman correlations Partial correlations adjusting for age, sex, and prespecified demographics FDR correction (Benjamini–Hochberg procedure, *q* < 0.05) Outlier identification and sensitivity analyses	Confirmatory
1c. Shift-and-persist coping strategies in relation to mental disorders	Patients with mental disorders, healthy participants	Examine whether individual differences in SAP coping strategies are associated with case–control status across multiple mental disorders and whether higher SAP are associated with a lower likelihood of belonging to patient groups than a shared non-clinical control group.	Exposure: Shift-and-persist coping strategies (quartiles; continuous in sensitivity analyses) Outcomes: case–control status within each mental disorder panel (patient vs non-clinical control) Covariates: age, sex, education, SES (childhood and current)	Chi-square tests, logistic regression (odds ratios, 95% confidence intervals), Cochran–Armitage trend tests, Firth-penalized logistic regression, FDR correction (Benjamini–Hochberg procedure, *q *< 0.05), sensitivity analyses	Confirmatory
1d. Metacognitive beliefs, CAS, and attentional control in relation to QOL and psychiatric symptoms	Patients with mental disorders, healthy participants	Examine whether metacognitive beliefs are associated with QOL via CAS, moderated by attention control, and identify CAS coping profiles.	Predictor: MCQ-30 (positive beliefs about worry and the negative beliefs about uncontrollability and danger of worry subscales) Mediator: CAS-1R (coping strategies subscale) Moderator: EC (attention control subscale) Outcomes: EQ-5D-5L (all groups); disorder-specific symptom severity (secondary outcomes)	Multi-group SEM (moderated mediation) LPA on the coping strategies subscale of the CAS-1R (six items): maximum likelihood with robust standard errors, model selection by the Bayesian information criterion, entropy, class interpretability Bolck–Croon–Hagenaars method (continuous outcomes)/DU3STEP (categorical outcomes) EQ-5D-5L minimal important difference-based deterioration (exploratory) Likelihood ratio tests, model fit indices comparison Supplementary LPA on MCQ-30 and EC Sensitivity analyses	Mixed

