## 1. Introduction

Mental disorders substantially diminish individuals’ quality of life (QOL) and impose high societal costs through losses in educational and employment opportunities, impaired interpersonal relationships, and reduced social participation [1]. The economic impact of mental disorders, including rising health care costs and productivity losses, has also attracted international attention [2], highlighting the need for rigorous evidence on the effectiveness and cost-effectiveness of mental health interventions [2,3]. However, treatment outcomes in mental health care are not adequately captured by symptom reduction alone [4]; comprehensive evaluation requires the explicit incorporation of patients’ subjective experiences, functional changes, and broader psychosocial dimensions [4,5]. Patient-reported outcomes (PROs) address this need by providing a standardized and scalable means of capturing patients’ own perspectives of their symptoms and health-related QOL, which can complement clinician-rated measures [6].

Evidence suggests that integrating PROs into clinical care improves outcomes and supports shared decision-making and quality improvement [7,8,9,10]. Nevertheless, the collection of data on PROs in mental health remains fragmented because of the use of different instruments, inconsistent assessment schedules, and misaligned data standards, resulting in siloed datasets and limited comparability [11]. A health registry directly addresses this fragmentation by providing a structured system for the collection, storage, and dissemination of standardized data from defined populations [12]. As health registries use harmonized instruments and aligned assessment schedules, they enable both individual-level integration and cross-study comparability. However, despite the inception of international initiatives such as Australia’s Mental Health National Outcomes and Casemix Collection and the OECD’s Patient-Reported Indicator Surveys [13,14], dedicated research registries for PROs in mental health remain scarce.

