### 2.2 Participants

Participants will be recruited in March 2026 from a nationwide web-based research panel managed by Macromill, Inc. (Tokyo, Japan). Recruitment will be conducted through direct invitations and study announcements posted on the Macromill website. The Macromill panel has been used in several previous studies [38,39]. Participants will be recruited using prespecified eligibility criteria and stratified quotas by diagnostic category. The provider maintains both general-population and disease-specific subpanels, including pre-identified panelists who have received physician diagnoses of the target disorders at medical institutions. Diagnostic classification will be based on the participant-reported history of physician diagnosis recorded in Macromill’s disease-specific panels, in which disease information is updated annually. By way of confirmation, invitees will additionally complete a screening item upon starting the survey to confirm their current diagnosis; diagnoses will not be independently verified through medical records or structured diagnostic interviews. Only respondents who pass their confirmation stage will proceed to the survey.

Inclusion criteria will be as follows: (1) understanding the study purpose and providing informed consent; (2) registration in a pre-identified disease-specific panel comprising individuals who have received a physician diagnosis of a target disorder and a positive response to an upfront screening item confirming a current diagnosis of one of the following conditions: major depressive disorder, social anxiety disorder, panic disorder, post-traumatic stress disorder, obsessive/compulsive disorder, insomnia, attention-deficit/hyperactivity disorder, autism spectrum disorder, type 1 diabetes, and type 2 diabetes; or registration as a healthy individual based on self-report indicating no current physician-diagnosed disease; (3) age ≥18 years; and (4) ability to respond in Japanese. Exclusion criteria will include the inability to provide informed consent or complete the survey.

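### Sub-study 1c adjusts its confirmatory SAP odds ratios for current SES and education, which may follow onset; report the odds ratio with and without them

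*Protocol article*

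**What the plan says.** In Table 1, the row for Sub-study 1c defines the outcome as "case–control status within each mental disorder panel (patient vs non-clinical control" and the exposure as "Shift-and-persist coping strategies (quartiles; continuous in sensitivity analyses". The directional part of the objective is "whether higher SAP are associated with a lower likelihood of belonging to patient groups than a shared non-clinical control group", and the analysis type is Confirmatory. The covariates are "Covariates: age, sex, education, SES (childhood and current". The planned methods are "Chi-square tests, logistic regression (odds ratios, 95% confidence intervals), Cochran–Armitage trend tests, Firth-penalized logistic regression", followed by Benjamini–Hochberg correction and sensitivity analyses.

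Timing follows from two other sections. Under 2.2 Participants, a patient enters only after "a positive response to an upfront screening item confirming a current diagnosis of one of the following conditions". Under 2.4 Measures, SES is a subjective rating (childhood and current) collected in that same cross-sectional survey. The Introduction says that mental disorders "impose high societal costs through losses in educational and employment opportunities, impaired interpersonal relationships, and reduced social participation". In the row for Sub-study 1b, current SES appears among the correlates and outcomes; one row later it is a covariate.

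**The concern.** Case status already exists when current SES is rated. If the disorder has lowered a patient's social position, current SES is partly a consequence of the outcome being modelled. If SAP is also related to current SES, putting SES in the logistic model conditions on a variable that depends on both, and the SAP coefficient is shifted. Attained education is open to the same question where schooling was interrupted or completed after onset.

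At stake is a prespecified directional conclusion in each disorder panel. All panels use one shared control group and one covariate list, so agreement between panels would not reveal the problem, and false-discovery-rate correction does not address it. The crude chi-square and trend tests adjust for nothing. They therefore do not provide the missing comparison, which is an odds ratio adjusted for age, sex and childhood SES but not for the later variables.

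**Working it through.** **The plan's own precision (2.6 Sample Size and Sampling).** For 200 and 300 per group, taking two-sided 5% and 80% power (not stated in that sentence):
- Half-width 1.96·√(0.25/n) = 6.93% and 5.66% (stated 6.9% and 5.7%).
- Detectable d = (1.96 + 0.84)·√(2/n) = 0.280 and 0.229 (stated 0.28 and 0.23).
- Detectable r by Fisher z = 0.197 and 0.161 (stated 0.20 and 0.16).

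These reproduce. A difference of d = 0.28 in SAP corresponds to an odds ratio of exp(−0.28) = 0.756 per SD, used below as the association the study is said to detect. The article gives no figure for the SAP odds ratio, the SAP–SES association or the disorder–SES association.

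**Bias formula.** Assume current SES = a·SAP + b·disorder + noise with residual SD 1. Let β be the SAP log odds ratio per SD without current SES. Given SAP, the log density ratio of SES between cases and controls is b·(SES − a·SAP) − b²/2. Adding current SES therefore changes the SAP coefficient from β to β − a·b. With a > 0 and b < 0 the shift is +a·|b|, toward or past the null.

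**Odds ratio per SD after adding current SES (a and b are assumptions):**

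| Without current SES | a=0.2, b=−0.5 | a=0.3, b=−0.8 | a=0.3, b=−1.0 |
|---|---|---|---|
| 0.90 | 0.995 | 1.14 | 1.21 |
| 0.80 | 0.88 | 1.02 | 1.08 |
| 0.756 | 0.84 | 0.96 | 1.02 |

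Example: exp(ln 0.80 + 0.2 × 0.5) = exp(−0.223 + 0.10) = 0.88.

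Full cancellation needs a·|b| of at least 0.105 for an odds ratio of 0.90, 0.223 for 0.80 and 0.28 for 0.756. If a = 0, nothing changes. If a = −0.2 and b = −0.5, 0.80 becomes 0.72, an exaggeration.

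**With the planned quartile coding.** A large simulation (1:1 cases to controls, childhood SES in both models) gave these top-versus-bottom quartile odds ratios without and then with current SES:
- 0.80 per SD, a=0.2, b=−0.5: 0.58 to 0.75.
- 0.90 per SD, a=0.2, b=−0.5: 0.79 to 1.02.
- 0.80 per SD, a=0.3, b=−0.8: 0.57 to 1.04.

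**What attenuation alone costs.** With 200 per group the standard error of the per-SD log odds ratio is about √(2/200) = 0.10. At 0.756, z = 0.28/0.10 = 2.8 and power is about 80%. After a shift of 0.10, z = 1.8 and power is about 44%. Simulating the two models, with continuous SAP and 5% per test, gave 79% and 39%.

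**The opposite structure.** Suppose instead that current SES precedes and influences both SAP (0.2 SD) and the disorder (log odds −0.4 per SD). With a true odds ratio of 0.80, omitting current SES gives 0.75 and adjusting gives 0.81.

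**The case against.** The best defence has four parts.

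First, the Introduction names lost educational and employment opportunities, not SES, and gives no size. A reader might infer that the protocol itself says mental disorders lower current SES. It does not; that step is an inference, and the instrument is a subjective rating. This stands.

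Second, a reader might infer that the adjustment will cancel or reverse the SAP association. The documents do not support that, because they give neither path. Under the assumed signs, attenuation is the likelier result at the detectable effect size, and a negative SAP–SES relation would act in the other direction. This also stands.

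Third, the objective is worded as an association, and the Discussion disclaims prespecified causal inference. Crude tests are planned, so a large gap between crude and adjusted results would be visible. This stands in part. A reader would see a gap but could not tell whether age, sex and childhood SES or the later variables produced it, and the row is still labelled Confirmatory with a stated direction.

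Fourth, current SES may be a genuine confounder, so a reader who concludes that it should simply be dropped goes too far; omission could bias in favour of the hypothesis. SAP is itself measured after onset, so no model here recovers an effect on onset. This stands and governs the fix.

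Table 1 also does not say that all covariates enter one model, and the full specifications are in supplementary materials that are not shown. If staged models are set out there, the remaining change is to say so in Table 1.

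**Conclusion.** The point holds in a limited form. A confirmatory, directional odds ratio is adjusted for one variable rated after cases already hold their diagnosis and for another that may have been completed after onset. That adjustment can bias the odds ratio, and the article lists no adjusted model without these variables.

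Under modest assumed paths (0.2 and −0.5 SD) the shift is 0.10 on the log-odds scale. That is enough to hide a weak association (0.90 to about 1.00) and to attenuate a moderate one (0.80 to about 0.88). An association of 0.756 would be reversed only with paths near 0.3 and −1.0 SD. Sign and size rest entirely on two associations that the documents do not give. Because current SES could be a consequence, a confounder or both, neither model is clearly right alone. This is an inexpensive improvement to the plan and not proof that the planned result will be wrong.

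**What to change.** In Table 1 and the supplementary specification, prespecify two logistic models for each disorder panel in 1c, using the same SAP coding:
- **Model A:** SAP, age, sex and childhood SES.
- **Model B:** Model A plus education and current SES.

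Report both odds ratios with confidence intervals side by side, and label B as adjusting for variables that may follow onset. State in advance that the confirmatory conclusion for a panel will be given together with any disagreement between A and B.

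The cost is wording and one extra model per panel, with no new data. Model A leaves some residual confounding by adult social position that childhood SES does not capture; the gap between A and B helps a reader judge how much the conclusion depends on that choice. The change should be made before results are seen.

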### 2.7 Statistical Analysis

To minimize information bias, we will conduct logic and range checks during data cleaning. Descriptive analyses will summarize distributions, floor and ceiling effects, and reliability indices. Unless otherwise specified, analyses will use two-sided tests, apply pre-specified multiple comparison correction strategies that differ by sub-study (see **Supplementary Materials**), and control for prespecified covariates (e.g., age and sex). Prespecified subgroup comparisons and corresponding interaction tests for diagnostic strata and sex will be conducted a priori, whereas other interaction analyses will be considered exploratory. Effect sizes with 95% confidence intervals will be reported, including Cohen’s *d *and Hedges’ *g* for continuous outcomes, odds ratios from logistic regression models, and standardized *β* coefficients for regression paths. Because the panel provider supplies only complete records for both the survey and the two-week retest, analyses will be restricted to complete-case data. Additional methodological details are provided in the **Supplementary Materials**.

In Sub-study 1a of Aim 1, all the analyses will be conducted in accordance with the Consensus-based Standards for the selection of health Measurement Instruments (COSMIN) guidelines [87]. The psychometric validation of the DQ5-J will include CFA to test the a priori unidimensional structure, with EFA reserved as a follow-up if the model fit is inadequate, internal consistency indices (Cronbach’s alpha and McDonald’s omega), test–retest intraclass correlation coefficients, model fit criteria, hypothesis-driven convergent and discriminant validity testing, and receiver operating characteristic analyses.

In Sub-studies 1b–1d of Aim 1, the correlations between the psychosocial factors and QOL/psychiatric symptoms will be examined by assessing the associations among the BPBs scores, SAP, SES, the psychiatric symptoms and sleep characteristics measures, and QOL using correlation analyses, linear regression models, and logistic regression. Sub-study 1d will additionally apply multiple-group structural equation modeling with moderated mediation and latent profile analysis to characterize the coping strategies assessed by the CAS-1R [88,89,90].

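### Sub-study 1d: if paths to EQ-5D-5L are compared between patients and healthy participants, unequal ceilings can produce a spurious difference, so a ceiling-aware sensitivity model is worth adding

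*Protocol article*

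**What the plan says.** All references are to the protocol article.

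- **Table 1, row 1d.** The population is "Patients with mental disorders, healthy participants". The main model is a "Multi-group SEM (moderated mediation"): metacognitive beliefs lead to QOL through coping (CAS-1R), moderated by attention control. The outcome entry is "Outcomes: EQ-5D-5L (all groups); disorder-specific symptom severity (secondary outcomes"), so EQ-5D-5L is the only outcome shared by patients and healthy participants. The analysis list also contains "Likelihood ratio tests, model fit indices comparison", without saying which constraints or groups these serve. The row is classed as mixed (part confirmatory, part exploratory).
- **Section 2.2.** The healthy group is defined by "registration as a healthy individual based on self-report indicating no current physician-diagnosed disease".
- **Section 2.7.** Ceilings appear once, as a summary: "Descriptive analyses will summarize distributions, floor and ceiling effects, and reliability indices". Effects are to be reported with standardised coefficients for regression paths. The general sensitivity analyses vary scoring, outcome thresholds, non-linearity of predictors and clustering parameters. A model for a capped outcome is not among them.
- **Section 2.5.** Full analytic specifications are referred to Supplementary Materials, which are not shown.

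**The concern.** A score with a top value cannot register differences among people who have reached it. When an outcome is capped, the fitted slope is roughly the underlying slope multiplied by the share of people below the cap. If two groups share the same underlying relation but differ in how many sit at the top, their fitted slopes differ.

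Row 1d is exposed to this because the healthy group is selected on something close to the outcome: absence of diagnosed disease, with a health-status score as the endpoint. That pushes the group towards the top of EQ-5D-5L. The risk is that 1d reports a weaker link between coping and QOL in healthy people than in patients when only the scale limit differs. The criteria that Section 2.6 names for SEM (fit, convergence, stability) would not expose this, because a worse fit under equal paths is exactly how the artefact would appear.

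**Working it through.** **Inputs from the article.** 200–300 participants per group (Section 2.6); two-sided tests (Section 2.7). The 5% level and, for the plan's own figures, 80% power are assumed, as the article states neither. It gives no figure for the multi-group SEM or for any ceiling share.

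**The plan's own figures.**
- Half-width: 1.96 × √(0.25/n) = 6.93% at n = 200 and 5.66% at n = 300.
- Detectable d: (1.960 + 0.842) × √(2/n) = 0.280 and 0.229.
- Detectable r: tanh[(1.960 + 0.842)/√(n − 3)] = 0.197 and 0.161.

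All agree with Section 2.6. None addresses comparison of paths between groups.

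**Step 1: attenuation.** Assume a true standardised path of -0.30 in both groups and cap the outcome so that a share c is at the maximum. Unstandardised fitted slope ≈ -0.30 × (1 − c):
- c = 20%: -0.24
- c = 50%: -0.15
- c = 60%: -0.12
- c = 70%: -0.09

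**Step 2: false rejection, unstandardised paths.** Simulation with identical true paths, 250 per group, heteroscedasticity-robust variance, two-sided 5% test, patient ceiling 20%:

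| Healthy ceiling (assumed) | Rejection of equal paths |
|---|---|
| 20% | about 5% |
| 30% | about 8% |
| 40% | about 15% |
| 50% | about 31% |
| 60% | about 52% |
| 70% | about 74% |

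Repeat runs agree to within one or two percentage points.

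**Step 3: the same data, standardised paths.** Capping also shrinks the outcome SD, to about 0.83 at a 20% ceiling and 0.50 at 60%. So -0.24/0.83 ≈ -0.29 in patients and -0.12/0.50 = -0.24 in healthy participants. The gap falls from 0.12 to 0.05. Testing equality on this scale rejects about 7–12% of the time over healthy ceilings of 50–70% (13–14% at 70% in some runs).

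**Step 4: a mediation model.** With assumed paths of 0.5 (predictor to mediator), -0.4 (mediator to outcome) and -0.1 (direct), the unstandardised mediator-to-outcome path shrinks to -0.36, -0.28, -0.20 and -0.12 at ceilings of 10%, 30%, 50% and 70%. False rejection at 200 and 300 per group:
- 10% v 30%: 16% and 21%
- 20% v 50%: 35% and 52%
- 10% v 70%: 89% and 97%
- no ceiling, or 10% in both groups: 4.5–5.6%

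**Step 5: are unequal ceilings plausible?** Put both groups on one normal latent scale with 20% of patients at the cap (cap at 0.84 SD). A healthy advantage of 0.5, 0.8 or 1.0 SD then puts 1 − Φ(0.84 − advantage) = 37%, 48% or 56% of healthy people there. These advantages are assumptions too.

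**Step 6: does a ceiling-aware model help?** A Tobit fit to the simulated data of Step 2 recovered -0.30 in both groups and rejected 4–6% of the time. The simulated errors were normal, as Tobit assumes.

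**The case against.** **No patient-healthy path test is written down.** The stated objective concerns an indirect association, its moderation and coping profiles. The likelihood ratio tests follow the latent profile items and may belong to them. This stands: a reader might infer that the comparison is a declared part of 1d, but it is only the natural reading of a multi-group model with one outcome for all groups. Section 2.7 (interaction tests for diagnostic strata) and the Discussion (direct comparison of patients with healthy participants) support that reading without settling it.

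**The large figures depend on the scale.** This stands. They apply to unstandardised paths, which multi-group equality constraints usually test. On the standardised scale named in Section 2.7 the effect is small. A reader might infer that 1d could find coping to matter in patients and not in healthy people; -0.29 against -0.24 does not support that.

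**The ceiling shares are assumed.** This stands. Having no diagnosed disease is not full health, and the Introduction says QOL impairment also occurs in the general population. At similar shares the problem vanishes, so it is too strong to say that the ceiling creates false differences.

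**The Supplementary Materials may already deal with it.** Possible. The article leaves the SEM specification to them, so its absence here is not an error. Nor does the article rely on robust standard errors for this: "maximum likelihood with robust standard errors" is attached to the latent profile analysis, and no SEM estimator is named.

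**A censored model is a choice, not a truth.** Also fair. It assumes unobserved health above the top score and a distribution for it, which argues for a sensitivity analysis rather than a replacement.

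**Conclusion.** The point holds as a conditional risk. Row 1d makes a bounded score the only outcome common to patients and to a group selected for having no diagnosed disease, and the article's stated response to ceilings is descriptive. If unstandardised paths are tested for equality between those groups and the healthy ceiling is clearly larger, a false difference becomes likely: about 31–74% at 50–70% v 20% with 250 per group. With a gap of 10–20 percentage points it is about 8–15%, and with equal ceilings nominal. On standardised paths it is modest, about 7–12%.

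This rests on assumed ceiling shares, an assumed path of -0.30, normal errors and, for these headline figures, a single-predictor model; the mediation model gives the same pattern. Comparisons among patient groups with similar ceilings, and the disorder-specific secondary outcomes, are much less affected. This is a cheap improvement, not a flaw that invalidates 1d.

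**What to change.** In Table 1, row 1d:

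1. Keep the planned EQ-5D-5L model.
2. State whether paths will be compared between patients and healthy participants, and on which scale.
3. Report the share at the EQ-5D-5L maximum by group.
4. For any such comparison, add a ceiling-aware sensitivity model (for example a censored or ordinal outcome), and claim a patient-healthy path difference only if it also holds in that model.
5. SWLS, already in the battery (Section 2.4), may be reported as a supporting outcome. It should not be an alternative route to the claim: it measures life satisfaction, and allowing either result to suffice would give two chances to declare a difference.

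If the Supplementary Materials already specify such a model, row 1d need only say so.

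The cost is plan wording and one extra model, with no new data. The downsides are heavier estimation, some global fit indices that are unavailable with a censored outcome, and dependence on that model's distributional assumption.
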